## Abstract

**Background:**

Heparin anticoagulation therapy is a widely used method to prevent cerebral vasospasm (CV) and venous thrombosis in patients with subarachnoid hemorrhage caused by ruptured cerebral aneurysms. Subcutaneous heparin injection is considered safe and effective, whereas continuous intravenous heparin infusion is still being debated due to the risk of bleeding. Although most retrospective studies have confirmed the safety and effectiveness of unfractionated heparin (UFH) after aneurysm embolization therapy and its ability to reduce CV, there is still no randomized clinical trial comparing UFH and subcutaneous low-molecular-weight heparin (LMWH) injection in this population. Therefore, this study aims to compare the clinical outcomes associated with these two treatment approaches.

**Methods:**

The study is an open-label, single-center, randomized controlled trial and aims to recruit 456 patients, with 228 patients in each group. The primary outcome was CV; the second outcomes measures are occurrence of bleeding events, ischemic events, heparin-induced thrombocytopenia, deep vein thrombosis, cerebral venous circulation time, brain edema score, and hydrocephalus incidence.

**Ethics and dissemination:**

This study protocol obtained ethical approval from the Ethics Committee of Baoan People’s Hospital, Shenzhen, Guangdong (approval number: BYL20220805). This work will be published in peer-reviewed international medical journals and presented at medical conferences.

**Trial registration:**

ClinicalTrials ID: NCT05696639. Registered on March 30, 2023.

**Supplementary Information:**

The online version contains supplementary material available at 10.1186/s13063-023-07493-9.

## Background

Aneurysmal subarachnoid hemorrhage (aSAH) is a highly fatal disease with a high incidence rate, accounting for about 80% of cases of SAH [1], and 46% of aSAH survivors suffer from long-term cognitive impairment [2]. Approximately one third of patients require lifelong care, which greatly affects their quality of life and places a tremendous burden on society [3].

Due to the complex pathophysiology of aSAH, it is often associated with ischemic and hemorrhagic complications. Although early treatment of aneurysms has become the primary means of preventing rebleeding, postoperative neurological complications are also common, including vasospasm, hydrocephalus, and rebleeding [4]. Cerebral vasospasm (CV) is the most severe and dangerous complication in the early stages of hemorrhage, typically occurring within 3–14 days following the onset of bleeding. The incidence of vascular spasm accounts for 40–70% of cases of aSAH and remains a significant factor contributing to morbidity and mortality [5]. It restricts blood flow and increases the risk of ischemia. Treatment options for CV include calcium channel blockers and endovascular therapy, as well as maintaining circulatory blood volume [6]. In addition to these treatments, the potential of heparin to reduce the incidence and mortality of aSAH-induced CV has gradually been explored, and it has also been shown to have anti-inflammatory and neuroprotective properties [7].

Unfractionated heparin (UFH) is a safe and commonly used anticoagulant, typically employed for the prevention of venous thrombosis and hypercoagulable states. It primarily functions by increasing the activity of antithrombin III to inhibit the activity of thrombin and factor Xa, thus preventing the formation of blood clots [8]. However, one of the side effects of heparin is bleeding, which necessitates coagulation function monitoring during its use.

In patients undergoing endovascular treatment for aSAH, continuous maintenance of arterial catheters with UFH during surgery contributes to the reduction of thrombus formation, while subcutaneous injections of low-molecular-weight heparin (LMWH) prevent formation of lower-extremity deep veinous thrombosis. However, both LMWH and UFH infusions have their pros and cons. Although neurocritical care guidelines recommend initiating subcutaneous heparin 24 h after aneurysm embolization surgery [9], the UFH injection has limitations due to its high molecular weight and low bioavailability. Intravenous UFH may, therefore, be considered more reliable.

Research indicates that low-dose intravenous UFH infusion yields favorable outcomes in reducing CV and ischemic complications. Multiple retrospective studies have demonstrated the safety and efficacy of low-dose continuous intravenous UFH infusion. However, there is controversy regarding the optimal dosage and duration of treatment. A retrospective study by J. Marc Simard revealed the safety of low-dose (8–9 U/kg/h) intravenous UFH administration in aSAH patients, without any cases of bleeding, heparin-induced thrombocytopenia (HIT), or deep vein thrombosis, and the incidence of clinical vasospasm significantly decreased compared to subcutaneous LMWH usage [10]. Another research by Markus Bruder in endovascular treatment for aSAH patients showed a lower probability of cerebral infarction when combining UFH with LMWH [11].

Regarding the timing of initiating of heparin, Annika’s study suggested that using heparin within 24 h after aneurysm repair might be safer and carry a lower risk of bleeding compared to initiating treatment 48 h later [12]. Randomized controlled trial results comparing subcutaneous injections of LMWH and intravenous infusion of UFH are currently lacking, although randomized controlled studies have shown the safe and effective reduction of CV and ischemia with subcutaneous injection of enoxaparin compared to placebo in patients with aSAH [13].

This study is a single-center exploratory randomized controlled trial comparing the impact of low-dose intravenous infusion of UFH and subcutaneous injection of LMWH on the incidence of CV in aSAH patients. The outcomes to be assessed also include the occurrence of bleeding events, ischemic events, HIT, deep vein thrombosis, cerebral venous circulation time, brain edema score, and hydrocephalus incidence.

### Trial status

The protocol version number for this experimental design is BYL20220216. The recruitment for the experiment is scheduled to commence in December 2023, with an estimated completion date for recruitment by December 2025.

## Methods

### Study design

This is a prospective, single-center, double-blind, randomized controlled trial. The protocol has been approved by the Ethics Committee of Shenzhen Baoan People’s Hospital (BYL20220805) and registered on ClinicalTrials.gov (NCT05696639). The trial will be conducted at a tertiary teaching hospital in Shenzhen, Guangdong Province, China (Shenzhen Baoan People’s Hospital). This hospital covers an area of approximately 40,000 square meters and has more than 1000 beds, serving a population of approximately 580,000 million residents (data revised in 2020), and the study protocol follows the SPIRIT checklist. The schedule for participant enrollment, intervention, and assessment is based on the SPIRIT figure (Fig. 1).

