### Study intervention

#### Randomization and blinding

This is a randomized, double-blind, controlled trial in which participants will be randomly assigned to one of two groups: the UFH group and the LMWH group. Participants will be unaware of their treatment assignment. The study aims to recruit 286 patients, with 143 patients in each group. Randomization will be conducted using a randomization sequence generated by R software. The specific method for randomization is as follows: install and load the rlist package, generate participant IDs, and use the shuffle function to randomize the participant IDs. The randomized ID data will then be arranged in order, with IDs 1–143 assigned to the UFH group and IDs 144–286 assigned to the LMWH group. Randomization will be performed by an assistant who is not involved in the study, and detailed information regarding the allocation will be kept in sealed envelopes labeled with a sequence number and will not be disclosed to participants. Data evaluation and analysis will be conducted by independent researchers under the supervision of an independent statistician. Participants, data-collecting researchers, and follow-up teams are precluded from making group allocations.

Severe adverse events include shock caused by thrombocytopenia and cerebral hemorrhage. If a severe adverse event occurs, the intervention should be discontinued if necessary, and the patient should receive appropriate rescue treatment. Blinding will be opened, and the event will be reported to the institutional review board. Compensation will be provided to subjects who are injured as a result of participating in the trial. Medical data will still be collected and analyzed. If a general adverse event occurs, patients do not need to be unblinded.

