### Interventions, administration and duration

As part of the trial design, all enrolled patients will receive intervention following embolization of the aneurysm. The UFH group will start intravenous infusion of UFH 24 h after the embolization procedure, upon confirmation of inactive bleeding through head CT scan. The heparin will be administered at a dose of 8–10 U/kg/h, and APTT values will be monitored twice a day for 7 consecutive days. The infusion rate of heparin will be adjusted based on APTT values to maintain it within the range of 35–45 s. In case of APTT values exceeding or falling below the set range, the infusion rate will be decreased or increased by 1 IU and maintained for 12 h. As per FDA standards for the use of low molecular weight heparin, the UFH group will receive subcutaneous injection of prophylactic dose of LMWH (4000 IU) every 12 h for a duration of 1 week starting 24 h after the aneurysm repair.

All experimental UFH is stored in original packaging at 15–30 °C (protected from light and heat). LMWH is stored at 2–8 °C. After opening for more than 24 h, heparin should be discarded. During the administration process, the nursing staff is trained on medication usage and provided with dosing instructions and adverse reaction management plans for both the UFH and LMWH group. To ensure blinding, any communication between the research staff and participants that may reveal group allocation should be avoided. The identity of the medication provider should also not be disclosed.

During hospitalization, both groups of patients will be closely monitored for vital signs and symptoms in the intensive care unit. Platelet-inhibiting agents, nonsteroidal anti-inflammatory drugs, and oral anticoagulants are prohibited during the patient’s treatment period. Physicians will check for interactions with heparin when using other medications and closely monitor bleeding symptoms, adjusting the dosage of heparin or other medications as needed. All patients will receive oral nimodipine, and the blood volume will be maintained in equilibrium. The intracranial pressure of all patients will be monitored with the transducer. Transcranial Doppler (TCD) ultrasound will be performed daily to evaluate for CV, and a weekly follow-up head CT will be performed. In cases where CV or increased intracranial pressure is suspected, urgent head CT angiogram (CTA) or CT scans will be performed for confirmation.

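### The article calls the trial both open-label and double-blind, describes nothing that could mask a titrated infusion, and states no blinded assessor for cerebral vasospasm

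*Protocol article*

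**What the plan says.** The blinding status appears in three places in the Protocol article.

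- Abstract, Methods: "The study is an open-label, single-center, randomized controlled trial and aims to recruit 456 patients".
- Study design: "This is a prospective, single-center, double-blind, randomized controlled trial".
- Randomization and blinding: "This is a randomized, double-blind, controlled trial in which participants will be randomly assigned to one of two groups", followed by "Participants will be unaware of their treatment assignment". The same section has the blind opened after a severe adverse event, and Intervention discontinuation adds an emergency unblinding procedure.

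Interventions, administration and duration sets out the treatment: "The UFH group will start intravenous infusion of UFH 24 h after the embolization procedure", with the rate adjusted to an APTT range, and "APTT values will be monitored twice a day for 7 consecutive days". To keep the blind, the article relies on sealed envelopes, confidential allocation, avoiding communication that could reveal the group, and not disclosing who provides the medication. Nurses hold dosing instructions for both groups.

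Primary and secondary outcomes builds CV from significant neurological deficit, Doppler thresholds (120 cm/s, or a Lindegaard ratio above 6) and arterial narrowing on CT angiography. Doppler is scheduled daily for all patients. Angiography is not scheduled: "In cases where CV or increased intracranial pressure is suspected, urgent head CT angiogram" or CT is performed.

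**The concern.** A reader cannot tell which design will be run, and one of the two labels must be wrong. The label matters because the primary outcome is partly a matter of judgement. Someone decides whether a deficit is significant, someone decides that CV is suspected and orders angiography, and someone reads the images. If those people can see which patients have an infusion pump and twice-daily APTT draws, CV can be looked for harder, or called more readily, in one group. That would create or hide a difference with no pharmacological cause, and no later analysis would reliably remove it.

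**Working it through.** **1. The label.** The abstract says open-label. Study design and Randomization and blinding say double-blind. All three are current text, so this is not a difference between a log of changes and the text it replaced. The contradiction stands.

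**2. Can the described measures mask the treatment?**

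| Measure described | What it protects | Hides the infusion? |
|---|---|---|
| Sealed numbered envelopes, confidential allocation | Concealment of allocation | No |
| No communication that reveals the group | Verbal disclosure | No |
| Medication provider not disclosed | Source of the drug | No |
| Placebo infusion, dummy injection, sham titration | Would mask the route and rate changes | None described |

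The Interventions section also gives the LMWH injections to the UFH group and states no regimen for the LMWH group. That conflicts with the comparison announced in the Background, and the passages must be reconciled. It does not affect this point: on either reading, the groups as described differ by a visible, titrated infusion.

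**3. Who is stated to be unaware of the arm?**

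| Assessment | Unaware of the arm? |
|---|---|
| Baseline data | Yes, two researchers (Baseline assessment) |
| Brain edema score (SEBES) | Yes, two blinded neurologists (Outcome assessments) |
| Data evaluation and analysis | Independent researchers; blinding not stated |
| Doppler, CT angiography and deficit judgement for CV | Not stated |
| Decision to order angiography | Made on clinical suspicion; blinding not stated |

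**4. What a detection gap would do.** The article gives no figure to reproduce here, so this is an illustration.

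Inputs:
- CV rate of 60%, the subcutaneous LMWH figure quoted in Sample size estimation.
- Two-sided α of 0.05, from the same section.
- Dropout of 10%, from the same section.
- Group size: the article gives both 228 (abstract and Sample size estimation) and 143 (Randomization and blinding). Less 10%: 228 × 0.9 = 205.2, taken as 205; 143 × 0.9 = 128.7, taken as 129.
- Detection gap of 5 or 10 percentage points with no true effect. This is an assumption; the documents give no basis for any size.

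The test is the two-proportion z-test with detected rates p₁ and p₂, difference d = p₁ − p₂ and mean rate p:

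SE₀ = √[2p(1−p)/n], SE₁ = √[(p₁(1−p₁) + p₂(1−p₂))/n]

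Rejection rate = Φ[(d − 1.96·SE₀)/SE₁] + Φ[(−d − 1.96·SE₀)/SE₁]

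Worked case, 60% v 55% at n = 205:
- SE₀ = √(2 × 0.575 × 0.425/205) = 0.0488
- SE₁ = √((0.24 + 0.2475)/205) = 0.0488
- Φ(−0.937) + Φ(−2.988) = 0.174 + 0.001 = 17.6% from unrounded values

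| Detected CV | 129 per group | 205 per group |
|---|---|---|
| 60% v 55% | 12.8% | 17.6% |
| 60% v 50% | 36.4% | 53.0% |

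The nominal rate is 5%.

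**The case against.** The strongest reply is that this is a condensed article. It refers to supplementary material and a full protocol that are not shown, and a dummy may be described there. This stands to the extent that one may not conclude that blinding is impossible, or that every participant will know the group; some participants may be too ill to consent for themselves. But the article does list how the blind is kept, nothing listed would work, and its own abstract says open-label. If a dummy exists, the abstract is wrong. If none exists, the other two sections are wrong.

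A second reply is that CV may depend little on judgement. Doppler is done daily in everyone against numerical thresholds, and the definition ends by saying that CV is counted whatever the patient's severity or clinical status. On that reading a deficit is not required. Yet the same definition opens with significant neurological deficits, so it is ambiguous, and the exposure is smaller on one reading than on the other. Angiography is triggered by suspicion on both.

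A reader might also infer that the brain edema score is the only assessment with blinded readers. The documents do not support that: Baseline assessment names researchers unaware of the group, and evaluation is given to independent researchers. None of these is stated to judge CV without knowledge of the arm.

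Finally, the size of any detection gap is unknown. That is correct, and the percentages show sensitivity rather than a predicted bias.

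**Conclusion.** The concern holds in this form: the blinding status is contradictory, participant and ward-staff blinding cannot exist as described, and no assessor of the primary outcome is stated to be blinded. The first part rests on the text alone. The second is limited to the measures the article lists. The third does not mean that CV will be judged unblinded, only that nothing stated prevents it.

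On size, a 5-point detection gap would raise the false-positive rate from 5% to about 13% to 18%, and a 10-point gap to about 36% to 53%, across the two group sizes the article gives. These figures assume no true effect, a 60% rate in one group, 10% dropout and the stated gaps. This should be settled before recruitment, because it concerns a core design property and the integrity of the primary outcome.

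**What to change.** 1. State one blinding status in the abstract, Study design, and Randomization and blinding, and name who is blinded and who is not. With the interventions as described, that is open-label treatment with blinded outcome assessment, and the statement that participants are unaware is removed. If masking does exist, describe it and correct the abstract instead.
2. Keep the adverse-event reporting steps. Reword the unblinding text around them to fit the chosen status; do not delete it, because the same text carries reporting to the review board.
3. Have CV classified from the recorded Doppler values, any CT angiography and the recorded deficit, with the arm removed, by blinded assessors the trial already uses. State whether a deficit is required.
4. Add a supportive sensitivity analysis using the daily scheduled Doppler thresholds alone. Label it as a different endpoint. It is needed because masked reading does not undo an angiogram ordered on unmasked suspicion. It does not make the bedside Doppler operator blind.
5. Reconcile the passages on which group receives the LMWH injections.

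The cost is wording, removal of arm labels from records, some added reading work for existing assessors (more if daily Doppler records are reviewed in full), and loss of the double-blind label.

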**Fig. 1 Fig1:**
[figure not shown]
Flowchart of the trial

### Participants

The recruitment program for participants is scheduled to commence in the year 2023 and is expected to conclude by December of 2025. Enrolled patients will be admitted to a neurosurgical monitoring ward and receive medical treatment according to the Guidelines for the Management of Aneurysmal Subarachnoid Hemorrhage [2]. The study process and schedule for outcome assessment are presented in Fig. 1 and Table 1.

**Table 1 Tab1:**
[figure not shown]
The schedule of enrolment, interventions, and assessments

### Inclusion criteria

Aged 18–70 yearsDiagnosis of aSAH from anterior communication circulation single aneurysmAdmission to the hospital within 72 h of the onset of symptomsUnderwent the endovascular treatment of the ruptured aneurysmWritten informed consent obtained from the patients

### Exclusion criteria

Posterior communication circulation aneurysmContraindication to heparin therapy, such as active bleeding or severe thrombocytopeniaRenal failure, malnutrition, and malignant tumorPregnant patients

#### Recruitment

In order to ensure the recruitment of a sufficient number of anticipated participants, our research team will collaborate with a network of 27 community health centers affiliated with Baoan People’s Hospital Group. This partnership will enable us to enlist a greater pool of potential eligible patients for inclusion in the study, and suitable participants will be selected based on predetermined inclusion and exclusion criteria. The screening logs will be maintained to document reasons for candidate exclusion. The consent process will follow the guidelines outlined in the Helsinki Declaration and the Good Clinical Practice International Coordinating Committee. Participants will receive an informed consent form that explains the study purpose, procedures, risks, and benefits and will be given adequate time to consider participation. For participants who are unable to provide their own consent, a legally authorized representative will do so on their behalf. Participants who meet the inclusion criteria and provide informed consent will be randomized to one of two groups using software-generated randomization sequences. Group allocation information will be kept confidential for the entire study period and only disclosed in special circumstances to prevent bias.

### Study intervention

#### Randomization and blinding

This is a randomized, double-blind, controlled trial in which participants will be randomly assigned to one of two groups: the UFH group and the LMWH group. Participants will be unaware of their treatment assignment. The study aims to recruit 286 patients, with 143 patients in each group. Randomization will be conducted using a randomization sequence generated by R software. The specific method for randomization is as follows: install and load the rlist package, generate participant IDs, and use the shuffle function to randomize the participant IDs. The randomized ID data will then be arranged in order, with IDs 1–143 assigned to the UFH group and IDs 144–286 assigned to the LMWH group. Randomization will be performed by an assistant who is not involved in the study, and detailed information regarding the allocation will be kept in sealed envelopes labeled with a sequence number and will not be disclosed to participants. Data evaluation and analysis will be conducted by independent researchers under the supervision of an independent statistician. Participants, data-collecting researchers, and follow-up teams are precluded from making group allocations.

Severe adverse events include shock caused by thrombocytopenia and cerebral hemorrhage. If a severe adverse event occurs, the intervention should be discontinued if necessary, and the patient should receive appropriate rescue treatment. Blinding will be opened, and the event will be reported to the institutional review board. Compensation will be provided to subjects who are injured as a result of participating in the trial. Medical data will still be collected and analyzed. If a general adverse event occurs, patients do not need to be unblinded.

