### Sample size estimation

The primary outcome of this study was the incidence of CV. J. Marc’s research indicated that the incidence of CV was 58% and 60% in the groups receiving intravenous unfractionated heparin and subcutaneous low molecular weight heparin, respectively [10]. The hypothesis was that the unfractionated heparin protocol was superior to the subcutaneous low molecular weight heparin injection in reducing the incidence of CV. The sample size of the study was calculated using a bilateral test to achieve a target effect of 0.1 and an α error of 0.05. Considering a dropout rate of 10%, each group would require 228 patients, so a total of 456 participants will be enrolled. The sample size was estimated using PASS (version 15.0.3, NCSS, LLC, Kaysville, Utah, USA).

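### The protocol gives two recruitment targets, 456 and 286, and fixes the allocation list at 286, so 170 of 456 participants have no allocation and the implied power depends on which section is followed

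*Protocol article*

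**What the plan says.** Three places in the protocol article give a size for the same two-arm trial.

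- **Abstract, Methods:** the trial "aims to recruit 456 patients, with 228 patients in each group".
- **Sample size estimation:** "each group would require 228 patients, so a total of 456 participants will be enrolled". The stated basis is a superiority hypothesis for unfractionated heparin (UFH), 10% dropout, and a calculation "using a bilateral test to achieve a target effect of 0.1 and an α error of 0.05". A cited study is reported as showing that the "incidence of CV was 58% and 60% in the groups receiving intravenous unfractionated heparin and subcutaneous low molecular weight heparin, respectively". No power is given.
- **Randomization and blinding:** "The study aims to recruit 286 patients, with 143 patients in each group". The IDs are shuffled once and then split, "with IDs 1–143 assigned to the UFH group and IDs 144–286 assigned to the LMWH group".

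Neither figure is labelled as superseded, as an interim stage or as a count of evaluable patients. No section provides for extending the list.

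**The concern.** The 286 is not an isolated slip. The total, the per-group count and both ID ranges in the randomization section agree with one another and disagree with the other two sections. It is also the section that the person generating the list will work from.

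The two instructions cannot both be carried out. A team following the randomization section stops at 286. A team following the sample size section has no allocations left after participant 286 and must add some by a step that the protocol does not describe. The size at which recruitment ends determines power and precision, so it should be a single number fixed in advance.

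**Working it through.** **1. The two sizes.** 2 × 228 = 456 and 2 × 143 = 286, so each total is consistent with its own per-group figure. The shortfall is 456 − 286 = 170, or 85 per group, and 170/456 = 37%. This step needs no assumption.

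**2. Could 286 be the evaluable part of 456?** 456 × 0.90 = 410, so no.

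**3. Can the planned 228 per group be reproduced?** Inputs from the sample size section: two-sided α = 0.05, target effect 0.1, 10% dropout, cited rates 60% and 58%. *Assumptions:* power of 80% or 90%, since none is stated, and the effect of 0.1 read as an absolute difference, since no scale is given. With p̄ = (p₁ + p₂)/2,

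n per group = [1.96·√(2p̄(1−p̄)) + z_power·√(p₁(1−p₁) + p₂(1−p₂))]² / (p₁−p₂)²

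| Rates | Power | n per group | After dropout (n/0.9) |
|---|---|---|---|
| 60% v 50% | 80% | 388 | 432 |
| 60% v 50% | 90% | 519 | 577 |
| 60% v 58% | 80% | 9,493 | 10,548 |

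For the first row: [1.96·√(2·0.55·0.45) + 0.842·√(0.24 + 0.25)]² / 0.01 = 387.3, rounded up to 388. With a continuity correction it becomes 408, or 454 after dropout.

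No two-sided superiority variant tried gives 228 or 143 per group at 80% or 90% power. Two calculations come close to 228 or 456, but each needs a reading that the text contradicts:
- Non-inferiority with a margin of 0.10, one-sided α 0.05, 80% power and rates of 60% and 58% gives 208 per group, or 229–232 after dropout. The stated hypothesis is superiority with a two-sided test.
- Continuity-corrected 58% v 48%, two-sided, 80% power gives 410, or 456 after dropout. That is 456 per group, not in total.

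**4. What each size delivers.** Evaluable per group after dropout: 228 × 0.9 ≈ 205 and 143 × 0.9 ≈ 129.

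Power = Φ{[|p₁−p₂| − 1.96·√(2p̄(1−p̄)/n)] / √([p₁(1−p₁) + p₂(1−p₂)]/n)}

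For 60% v 50% with n = 205: (0.100 − 1.96 × 0.0491)/0.0489 = 0.075, and Φ(0.075) = 53%.

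| Total | n per group | Power, 60% v 50% | Power, 60% v 58% | Difference from 60% detectable with 80% power |
|---|---|---|---|---|
| 456 | 228 (no loss) | 57% | 6% | 13.1 points |
| 456 | 205 (10% loss) | 53% | 6% | 13.8 points |
| 286 | 143 (no loss) | 40% | 5% | 16.5 points |
| 286 | 129 (10% loss) | 36% | 5% | 17.4 points |

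The 60% v 50% column rests on the assumed meaning of the target effect. The 60% v 58% column uses the cited rates as they stand.

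**The case against.** The contradiction itself is hard to dispute. The objections concern what follows from it.

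- *A reader might infer that the conflict leaves the trial's power undefined.* The document does not support this. The sample size section states no power for any size, so power would be unstated even if every section said 456. It can also be computed for each size once rates are assumed. What the conflict adds is that the implied power depends on the section followed. This objection stands.
- *A reader might infer that 456 is right because the sample size section derives it.* Two of the three places do agree on 456, and 286 may be left over from an earlier draft, but nothing in the document confirms that. The stated inputs do not yield 228 per group at 80% or 90% power, so 456 is asserted rather than derived. This objection also stands, and it changes the fix.
- *The power contrast depends on a chosen pair of rates.* This is fair: 60% v 50% appears nowhere in the document. At the cited 60% v 58%, the choice of size hardly alters power. The shortfall of 170 (37%) depends on no such choice.
- *A reader might infer that the sponsor could choose its stopping point after seeing data.* The document describes no such plan. Two published targets leave that question open, but no intent can be read into them. A longer list generated before enrolment would not be ad hoc.
- *An article condenses a fuller protocol.* This does not help. Nothing is alleged to be missing; two stated values conflict, and no further document could make both true.

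**Conclusion.** The point holds as an internal inconsistency that must be resolved before the plan can be carried out. The protocol sets recruitment at both 456 and 286, and its list covers only 286, leaving 170 participants (37% of 456) without an allocation.

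Under the assumed 60% v 50%, the choice of size moves power from about 53–57% to 36–40%. It moves the difference detectable with 80% power after dropout from about 14 to about 17 points. At the cited rates, power is about 5–6% either way. Neither size gives 80% power for a 10-point difference, so adopting 456 would remove the contradiction but would not make the trial adequately powered for that effect. The document does not show which size is intended.

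**What to change.** 1. Before the first enrolment, the sponsor confirms which size is intended and states that one number in the abstract, in Randomization and blinding and in Sample size estimation.
2. The allocation list and the ID ranges in the text are regenerated for that number. If enrolment has already begun, this should be a documented amendment made before any look at outcomes.
3. Sample size estimation states the two assumed CV rates, the scale of the 0.1 effect, and the power or detectable difference that the chosen size delivers. On the assumptions above and after dropout, the detectable difference with 80% power is about 14 points for 456 and about 17 points for 286. The section should not present 456 as following from the inputs now given.

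The cost is protocol wording, one rerun of the list generator and a less favourable stated power. Resolving this point requires no enrolment beyond the 456 already stated.
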